## Abstract

Background: There are limited treatment options for mental health comorbidities associated with Inflammatory Bowel Disease (IBD), although they have been shown to negatively affect the course of IBD and multiple important areas of functioning. Photobiomodulation (PBM) is a new therapeutic intervention using laser-generated low-powered light therapy that has shown early promise in alleviating fatigue, depression, and pain in chronic illness. Methods: This prospective, single-arm pilot study aims to assess the feasibility and efficacy of PBM in the treatment of fatigue, depression, and pain in youth with IBD. We will recruit 28 young adults with IBD who will receive PBM in addition to treatment as usual. The primary outcome will be fatigue, while secondary outcomes will include depression, pain, quality of life, inflammatory markers, alterations in microbiome composition, physical activity, and functioning. Outcome measures will be assessed at baseline, after a 10-week control period (pre-PBM), at 20 weeks (post-PBM), and at 30 weeks. Feasibility will be assessed by attendance, recruitment rates, and participants’ views of PBM. Mixed-effects linear regression modelling will be used to assess the PBM effect on continuous outcomes (fatigue, depression, anxiety and stress scores, and inflammation levels). Results: The study will provide preliminary indicators of PBM feasibility and efficacy in IBD.

## 1. Introduction

Inflammatory Bowel Disease (IBD) is an immune-mediated disease characterised by chronic inflammation of the gastrointestinal tract, and high levels of fatigue, depression, pain and other extraintestinal manifestations that worsen the course of IBD, impair quality of life and contribute to high burden of disease [1,2,3,4].

Fatigue prevalence rates range between 40–48% in remission, and up to 86% in moderate-to-severely active IBD [5]. The aetiology and persistence of IBD-related fatigue is likely to be multifactorial and associated with complex immune mechanisms including genetics, epigenetics, and environmental and drug treatment-related effects. Specifically, these factors include continuing low-grade systemic inflammation, IBD medication side effects, nutritional deficiencies, comorbid depression, and other comorbidities, such as joint pain, respiratory and cardiovascular disease, and poor sleep quality [6]. There is no known effective method of treating IBD-related fatigue [5,6].

Fatigue is likely mediated by both the central nervous system (CNS) and peripheral neuromuscular mechanisms [6]. In chronic disease, fatigue is associated with unrefreshing sleep, reduced physical functioning, and depression and is also part of depressive symptoms [6].

Depression rates in individuals with IBD during periods of remission are 2–3 times higher than in the general population, ranging between 24 and 27%, and several times higher during exacerbations with reported rates of depression during flares of over 60% [7]. Young adults with IBD have significantly higher rates of depression than their healthy peers and young people with other chronic conditions. Given the bidirectional relationship between depression and IBD [8], treatment of depression is likely to improve IBD symptoms and its prognosis. Since depression is strongly associated with the presence and severity of IBD-related fatigue and fatigue is a common symptom of depression [9], treating depression can improve fatigue and vice versa, and treatment of both can improve quality of life and IBD course. The impact of depression on fatigue is likely to be twofold as depression can both cause and worsen fatigue through reduced energy levels and anhedonia (the inability to feel pleasure in normally pleasurable activities), which are symptoms of depression, and through its impact on the IBD course [3,4,9]. 

Depression has been shown to be associated with IBD-related pain with multiple postulated mechanisms of their co-occurrence and interaction, including common underlying inflammatory pathways, amplification of pain signals by depression and stress and reduced adherence to medications [9,10]. One of the most common presenting symptoms of Crohn’s disease is abdominal pain, and one of the most frequently reported extra-intestinal symptoms of IBD is the pain of seronegative spondyloarthropathy affecting the large joints [11]. 

Since fatigue and depression in the setting of IBD are associated with an increase in IBD-related pain [10], successful treatments are likely to work through addressing their common underlying causes. However, there is no single effective treatment for these inter-related symptoms of IBD, and those which are used are most likely to be biologics or pharmacologically based, thus with the potential for side-effects, loss of efficacy or resistance. Photobiomodulation is, therefore, a promising novel alternative treatment option which may augment the treatment of IBD-related fatigue, depression, and pain.

## 2. Photobiomodulation in Treatment of Fatigue, Depression, and Pain

Photobiomodulation is the use of photonic (light) energy to regulate and enhance cellular functioning. The effect of PBM is thought to occur through the interactions of photons with the cytochrome c complex in mitochondria which leads to improved cellular metabolism and tissue regeneration. When used for pre-conditioning before exercise, PBM has been shown to have moderate evidence for improving physical performance [12,13] and low to moderate evidence for reducing muscle fatigue [13,14].

Additional beneficial effects of PBM on physical performance include reduced muscle fatigue in a variety of settings and conditions [15], most likely by increasing local matching of bulk and microvascular oxygen delivery relative to muscle oxygen utilisation [16]. 

The evidence for the use of PBM in the treatment of depression is emerging, with recent reviews identifying PBM as a promising novel treatment that has been well tolerated by people with depression [17,18]. In Parkinson’s disease, PBM has been shown to improve sleep-wake cycles [19] critical in improving fatigue symptoms. 

The effectiveness of PBM in managing pain has been well supported by research [20,21,22]. Author [name] has researched the effect of different wavelengths and doses of PBM in people with chronic pain and described the link between the peripheral application of PBM and central nervous system effects and analgesic mechanisms of PBM [23].

There is emerging evidence on the positive effect of PBM on the gut microbiome. Liebert et al. [24] have investigated PBM in a mouse model and demonstrated that PBM (red and infrared wavelengths) can alter microbiome diversity in healthy mice and increase numbers of *Allobaculum*, a bacterium associated with a healthy microbiome. Zanotta and colleagues [25] applied PBM to consenting participants with a history of oral mucositis following cancer therapies. They found that PBM modulated the inflammatory response by reducing the proinflammatory cytokines and changed the microbiome composition with increased diversity and an increase in the number of known beneficial bacteria. 

Taken together, these research results suggest that PBM can improve fatigue, depression, pain, and microbiome diversity in chronic disease. Despite this, there have been no trials or reviews of PBM in IBD to date apart from our group’s recent article on the mechanism of PBM in IBD [26]. This prospective, single-arm pilot study of PBM in youth with IBD will therefore assess the feasibility and preliminary efficacy of PBM in IBD. Should improvement in fatigue markers and/or depressive symptoms be found, the research will progress to a larger randomised, placebo-controlled study.

## 3. Study Goals, Objectives, and Hypotheses

The goal of this research is to determine the feasibility of progressing to a larger study regarding the possible effect of PBM for managing the symptoms of fatigue, depression, and pain experienced by young adults with IBD. 

The primary objective is to determine if the protocol and the intervention are acceptable to participants, and feasible to deliver. Acceptability/tolerability/feasibility of the intervention will be assessed quantitatively, through measures of attendance/attrition/drop-out and qualitatively, through assessing participants’ experiences and views of the intervention through the post-PBM evaluation questionnaire. In conjunction, we wish to understand if PBM (delivered per protocol) influences fatigue (measured using the FACIT-Fatigue questionnaire). The FACIT-Fatigue questionnaire has been validated for use in IBD [27].

The secondary objectives are to evaluate the effect of PBM on depression (measured using the short form of the Depression, Anxiety and Stress Scale DASS-21) and health-related quality of life (measured by the Short Form 36; SF-36); levels of inflammation (Erythrocyte Sedimentation Rate-ESR, C Reactive Protein-CRP and Faecal Calprotectin-FCP); the gut microbiome (by quantity and type of bacterial phyla and genera found in stool samples); abdominal and joint pain, physical activity (measured by the International Physical Activity Questionnaire-IPAQ), and physical function (Patient-specific Functional Scale). We will use data from this study to inform the design and sample size calculation for a future RCT. 

### Hypotheses

**Hypothesis** **1.***PBM intervention will be feasible and acceptable*.

**Hypothesis** **2.***PBM intervention will result in significantly improved fatigue scores post-intervention*.

**Hypothesis** **3.***PBM will decrease depression and increase QoL*.

**Hypothesis** **4.***PBM will result in decreased abdominal and joint pain, increased physical activity, and physical function*.

**Hypothesis** **5.***PBM intervention will be associated with decreased inflammatory burden*.

**Hypothesis** **6.***PBM intervention will be associated with an increase in the alpha diversity of the gut microbiome with an increase in the number of known beneficial bacteria and decrease in number of potentially pathogenic genera*.

## 4. Materials and Methods

This is a prospective, single-arm pilot study. The study is designed as a pre–post study with three phases, each with a duration of ten weeks, and four data collection points. The three study phases include a 10-week observation period, followed by a 10-week PBM intervention phase during which the participants will receive weekly PBM, and the study concludes with a second 10-week observation or washout phase. Data collection points include baseline, pre-PBM, post-PBM, and the final collection point, 10 weeks after the completion of the PBM intervention. The purpose of the post-intervention observational period is to record and evaluate any sustained effects of PBM. The study duration is expected to be up to 12 months, from commencement of recruitment to end of data collection of the final participant. Rolling recruitment will be used until the required sample of 28 is achieved. 

The primary outcome of interest will be fatigue while secondary outcomes will include depression, pain, quality of life, inflammatory markers, and microbiome characterisation (of phyla and genera), physical activity, and physical functioning. All outcome measures, other than pain, will be assessed at the 4 data collection points. Pain will be assessed weekly as evidence shows that this frequency will provide most accurate assessment. 

Feasibility of the study procedures and PBM intervention will be assessed by the participants’ attendance, their views of PBM, recruitment, and attrition rates. Mixed-effects linear regression modelling will be used to assess the effect of PBM on continuous, outcome measures. We will use the intention-to-treat principle in that we will include everyone in the analysis, whether they complete the treatment or not. We will also conduct sensitivity analysis that only includes those who completed the per-protocol intervention and will report the proportion of participants lost to follow-up.

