### PBM Safety

Photobiomodulation therapy (PBMt) is a safe, non-invasive, non-pharmacological method for treating a range of symptoms and signs across a range of conditions. Sensitivity to light has been reported in 2–15% of PBM trials participants, in the form of temporary dizziness, increase in pain, tiredness, or euphoria. Several studies have concluded that there are no long-term adverse effects of PBM in vitro [28], in vivo, including non-human primates [29], and in human models [30,31,32]. We therefore do not expect the participants to experience any adverse events. However, should this occur, the participants will be provided with advice and care by their doctor as required; the event will be recorded as part of the study outcomes; and the institutional human research ethics committee will be informed.

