
At the end of the treatment phase all questionnaires will be repeated, physical measures will be re-assessed, and self-report pain diaries retrieved from participants. Participants will be asked to complete the post-PBM evaluation survey to establish the acceptability/tolerability of the study requirements and intervention. The survey will contain a mixture of questions including open-ended free text questions regarding PBM acceptability and their views of any changes they experienced as a result of the intervention.

After the post-PBM appointment, participants will enter a second observational (no PBM treatment) period of 10 weeks during which they will continue to complete a weekly study pain diary.

The study will end after 30 weeks, when all questionnaires will be repeated, measures will be re-assessed (final blood and stool samples collected) and self-report diaries retrieved from participants before they exit the study.

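### The completer-only sensitivity analysis cannot show that the fatigue result is robust to dropout, and it would favour PBM if participants stop because they feel worse

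*Protocol article*

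**What the plan says.** Section 4 (Materials and Methods) of the protocol article sets the model, "Mixed-effects linear regression modelling will be used to assess the effect of PBM on continuous, outcome measures", and the analysis set, "We will use the intention-to-treat principle in that we will include everyone in the analysis, whether they complete the treatment or not". It then names one sensitivity analysis: "We will also conduct sensitivity analysis that only includes those who completed the per-protocol intervention". The only other item on non-completion is descriptive: the authors "will report the proportion of participants lost to follow-up".

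The PBM Safety section states: "Sensitivity to light has been reported in 2–15% of PBM trials participants, in the form of temporary dizziness, increase in pain, tiredness, or euphoria". Fatigue is the primary outcome and pain a secondary one (Section 4), and tiredness is among the FACIT-Fatigue items (Section 6.1).

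On timing, Section 6.1 says "At the end of the treatment phase all questionnaires will be repeated", and the Abstract places the later assessments at 20 and 30 weeks. Section 6.5 expects 5–10% dropout and plans to recruit 28.

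**The concern.** A sensitivity analysis should vary an assumption on which the main result depends. When week-20 scores are missing, a likelihood-based mixed model assumes that they follow the course predicted from that participant's observed scores and the rest of the sample. The doubtful case is a participant who did worse than predicted and was therefore not seen. Removing non-completers never examines that case.

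The design makes this matter more. There is no comparison arm to share the selection, so any link between completing and change in fatigue goes straight into the pre-post estimate among completers. Entrants already score below 30 on FACIT-Fatigue and must attend ten weekly sessions, so worsening fatigue is a plausible reason to stop. Two of the listed reactions overlap with efficacy outcomes.

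What is at stake is the reading of Hypothesis 2 (improved fatigue). If the two analyses agree, a reader may take the result as confirmed against dropout when that question has not been tested.

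**Working it through.** **1. The plan's own figure.** Inputs from Section 6.5: effect size 0.60, two-sided alpha 0.05, paired t-test, 80% power. Exact noncentral-t power is 78.5% at n = 23 and 80.4% at n = 24, so 24 is reproduced. Inflation gives 24/0.95 = 25.3, so 26, and 24/0.90 = 26.7, so 27. The planned 28 covers dropout up to 1 − 24/28 = 14.3%. The sample size is not in question. It supplies the scale (0.60 SD) and the dropout range used below.

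**2. What the completer analysis does with a non-completer.** There are two cases.

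- The person stops PBM but is assessed at week 20. The main analysis uses the score and the completer analysis discards it.
- The person stops PBM and has no week-20 score. The main analysis relies on the model's prediction, and the completer analysis drops the person.

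In neither case is a missing score given a value different from the model's prediction. This holds whatever the reason for stopping and needs no arithmetic.

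**3. Simple bound on the shift.** Let k of 28 not complete, with mean change m (in SDs of change, negative meaning worse), and let the full-sample mean be 0. Then k·m + (28 − k)·c = 0, so the completer mean is c = −k·m/(28 − k). The protocol gives no outcomes for non-completers, so m is assumed. Dropout of 5–10% of 28 is 1.4 to 2.8 people, taken as k = 1 to 3.

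| k | m = −1 | m = 0 | m = +1 |
|---|---|---|---|
| 1 | 1/27 = +0.04 | 0 | −0.04 |
| 2 | 2/26 = +0.08 | 0 | −0.08 |
| 3 | 3/25 = +0.12 | 0 | −0.12 |

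If the k people removed are always those with the worst change (simulated), the completer mean is +0.08, +0.14 and +0.20 SD for k = 1, 2 and 3. The chance of a significant result in favour of PBM with no true effect is then 6.9%, 13.6% and 22.5%. That is the limit, not the expectation.

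**4. Graded selection.** Assumptions: n = 28; change distributed N(μ, 1); logistic non-completion with slope 1 per SD worse change (odds ratio e¹ = 2.7), calibrated to the stated dropout; a t-test among completers at two-sided 5%, counting only rejections in favour of PBM.

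| Non-completion | Completer mean, μ = 0 | False improvement (nominal 2.5%) | Completer mean, μ = 0.60 |
|---|---|---|---|
| 5% | +0.05 SD | about 4% | 0.65 SD |
| 10% | +0.09 SD | about 6–7% | 0.69 SD |

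With non-completion at random, at the same rates, the shift is 0 and the false-improvement rate stays at 2.5%.

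The protocol gives no SD for change in FACIT-Fatigue, so these shifts cannot be put in scale points.

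**The case against.** The strongest reply is that this is a conventional plan in a condensed article: include everyone, add a per-protocol analysis, report losses. Further missing-data analyses may sit in a statistical analysis plan that is not shown. That stands as far as it goes, and nothing here rests on the absence of another analysis. The point concerns the analysis the article does name and the role it gives it.

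Several stronger readings are tempting, and the documents do not support them.

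- **That the completer analysis can only flatter PBM.** People may stop for unrelated reasons, giving no shift, or because they improved, giving a shift against PBM. The safety section never links the reactions to stopping, and its list, "in the form of temporary dizziness, increase in pain, tiredness, or euphoria", also includes euphoria.
- **That the main analysis errs in the same direction.** Section 4 keeps non-completers, and a mixed model uses each person's own observed scores. No bias in the main analysis has been calculated.
- **That stopping PBM means leaving the study.** No section says so. The end of the treatment phase can be read as the end of a fixed ten-week phase, not as a person's last session.
- **That Section 3 contradicts Section 4.** The phrase "we wish to understand if PBM (delivered per protocol) influences fatigue" can simply describe how PBM is given. Read as a per-protocol question, it gives the completer analysis a purpose of its own, but as a supplementary analysis.
- **That non-completion could reach 40%.** One could get there by requiring all ten sessions with a 5% independent chance of missing each (0.95¹⁰ = 60% completing). Both inputs are assumed, and random misses cause no bias.

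**Conclusion.** The point holds in a limited form. The stated sensitivity analysis selects on an event that can depend on the outcome, and it leaves untested the assumption that dropout puts in doubt. Its agreement with the main result would not be evidence of robustness. That conclusion follows from the structure of the analysis and needs no assumption about why people stop.

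The direction and size do need assumptions. If stopping is linked to worse fatigue as in step 4, the completer estimate shifts by about +0.05 to +0.09 SD within the protocol's own dropout range, against a design effect of 0.60 SD. The false-improvement rate becomes about 4–7% instead of 2.5%. If stopping is unrelated to outcome, the shift is zero. These figures describe the completer analysis only. They do not show that the main estimate, or an effect size carried from it into a later randomised trial, is biased.

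**What to change.** In Section 4:

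- Relabel the completer analysis as supplementary, describing outcomes among those who received the intervention as planned.
- Make the sensitivity analysis one that keeps all participants. Give missing week-20 FACIT-Fatigue values no change from pre-PBM, then progressively worse values, and report the point at which the conclusion changes.
- State that the week-20 and week-30 questionnaires of participants who stop PBM are included in this analysis. FACIT-Fatigue takes two minutes by the protocol's own account, so the added burden is small.

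The cost is a few sentences and a few extra model runs. The drawback for the authors is a robustness result that may be less favourable than the completer analysis.

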### 4.1. Recruitment

Participants will be recruited from the IBD and Young Adult Support outpatient clinics at Mater Health from the patient lists of two of the study investigators (TE, JB). The study will employ rolling recruitment until the sample size of 28 participants is reached. Recruitment will be initiated during outpatient appointments, and those who are interested will meet with the research assistant/investigator who will explain the study in more detail, conduct the initial screening, and for those interested in taking part, organise the initial appointment when written informed consent is gained.

### 4.2. Participant Selection

Since this is a study of PBM in young adults with IBD, main eligibility criteria will include participants’ age, confirmed IBD diagnosis and the presence of fatigue. 

Inclusion Criteria: Age 18–35 years.Diagnosis of IBD made by gastroenterologist.Fatigue symptoms (FACIT F score < 30).Verbal and written English proficiency that will enable them to participate.Ability to provide informed consent.Patients of the IBD outpatient clinics at Mater Hospital.Individuals who are able to attend the 10 weekly PBM treatment sessions as well as the additional sessions at the baseline and at the end of the study.

Exclusion Criteria:

Individuals with major psychiatric illness (psychosis, Post-Traumatic Stress Disorder, substance abuse/dependence) as its treatment and symptoms could prevent participation in the programme.Individuals without conversational or written English.Major surgery booked in the next 6 months as this would preclude participation.Pregnant women, as there are no studies to date of PBM in pregnancy.

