### 6.5. Sample Size Calculation

We have calculated that the sample size required to achieve 80.0% power to reject the null hypothesis, for the effect size of 0.60 and a significance level (alpha) of 0.050, using a two-sided paired t-test, will be 24. From researchers’ experience, the most likely dropout rate in this type of study is between 5–10%. Considering the 5–10% dropout, we will therefore aim to recruit a total sample size of 28.

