## 7. Discussion

The study will advance the knowledge about the feasibility and acceptability of PBM in IBD and provide data on the preliminary effectiveness of PBM on fatigue, depression, pain, microbiome diversity, and quality of life in individuals with IBD. The study results will be utilized to determine whether further research is required (based on the potential efficacy of the intervention) and the optimal sample size and design for a future RCT. 

This study is the first to assess PBM intervention in youth with IBD who experience high levels of fatigue, depression, pain and significantly impaired quality of life. Potential benefits of PBM may be particularly relevant in youth with IBD as they could affect their future education, employment, social and overall functioning, and long-term prognosis. 

The study will be using a PBM protocol adapted for individuals with IBD from previous PBM research in other cohorts that, if proven feasible, may become integrated into the treatment pathways for IBD. 

This study has the potential to validate PBM as a feasible intervention for fatigue, depression, and pain in IBD and translate this approach to other chronic diseases. The inclusion of both self-reported psychosocial and physical outcomes may provide additional insights into the relationship between IBD, fatigue, depression, and pain and their responses to PBM.

As this is a pilot, single-arm study, we will not be able to exclude the placebo effect, as any positive results could be due to treatment, placebo, or a combination of the two. To minimise the effect of this, the study will have a 10-week non-intervention period, followed by the 10-week PBM intervention. The 10-week post-intervention period will attempt to elicit whether any ongoing improvements will remain. We anticipate that any positive results would need to be followed up with an RCT with an adequate sample size, updated recruitment strategies, and study procedures.

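### The major-surgery exclusion looks 6 months ahead (about 26 weeks) but participation lasts 30 weeks, so surgery booked for roughly weeks 27 to 30 is not excluded by that criterion

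*Protocol article*

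**What the plan says.** The exclusion list in section 4.2 of the protocol article bars people with "Major surgery booked in the next 6 months as this would preclude participation". The inclusion list in the same section asks for ability to attend the ten weekly PBM sessions "as well as the additional sessions at the baseline and at the end of the study".

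Section 4 sets out three consecutive ten-week phases: observation, PBM, and a second observation or washout. Section 6.1 confirms the total: "The study will end after 30 weeks". At that last visit the questionnaires are completed again and the final blood and stool samples are taken. During the washout the only other data are pain scores, since "they will continue to complete a weekly study pain diary".

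The last phase has a declared role. Section 4 says: "The purpose of the post-intervention observational period is to record and evaluate any sustained effects of PBM". Section 7 repeats the point: "The 10-week post-intervention period will attempt to elicit whether any ongoing improvements will remain".

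**The concern.** The surgery criterion is justified by participation, so its window should be at least as long as participation. It is not: it ends before the final visit.

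Week 30 is the only full assessment after the washout, so it carries the evidence on whether any improvement lasts. In someone who has just had a major operation, fatigue, pain, ESR, CRP, faecal calprotectin and stool microbiome could all be disturbed by the operation. Post-operative worsening would make a sustained benefit look smaller than it is. The study has a single arm, so no concurrent control group would reveal this.

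The analyses described in section 4 would not remove such a person. The main analysis keeps everyone. The sensitivity analysis is restricted to those who completed the intervention as planned, and a participant operated on in weeks 27 to 30 finished PBM by about week 20. Eligibility is therefore the natural place to act.

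**Working it through.** **Inputs**

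- Exclusion window: 6 months (section 4.2).
- Participation: three phases of 10 weeks (section 4), ending at 30 weeks (section 6.1).
- Sample size: 24 needed, 28 to be recruited; planning effect size 0.60 (section 6.5).
- Assumed, because the document gives no figure: number of affected participants (one), size of the surgical shift (k = 1 or 2 SD of the change score), and time from screening to baseline.

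**Length of participation.** 3 × 10 = 30 weeks, which reproduces the protocol's figure. In months: 30 × 7 = 210 days; 210 / (365.25/12) = 6.9 months.

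**Length of the window.** 365.25/2 = 182.6 days; 182.6/7 = 26.1 weeks. By calendar, six months is 181 to 184 days, or 25.9 to 26.3 weeks.

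**Gap, counted from baseline.** 30 − 26.1 = 3.9 weeks, roughly weeks 27 to 30.

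**Gap if the six months run from screening.** Section 4.1 places initial screening before the baseline appointment but gives no interval. For an assumed interval of s weeks the gap is 30 + s − 26.1:

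| s (assumed, weeks) | Gap (weeks) |
|---|---|
| 0 | 3.9 |
| 1 | 4.9 |
| 2 | 5.9 |
| 4 | 7.9 |

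**What the window does cover.** Counted from baseline it covers the control period, the whole PBM phase, the post-PBM assessment at week 20, and 26.1 − 20 = 6.1 weeks more. The week-20 assessment would be exposed only if screening preceded baseline by more than about 6.1 weeks.

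**Effect of one affected participant.** A shift of k SD in one of n participants moves the mean by k/n SD:

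| n | k (assumed) | Shift in mean (SD) | Relative to 0.60 |
|---|---|---|---|
| 28 | 1 | 1/28 = 0.036 | 6.0% |
| 28 | 2 | 2/28 = 0.071 | 11.9% |
| 24 | 1 | 1/24 = 0.042 | 6.9% |
| 24 | 2 | 2/24 = 0.083 | 13.9% |

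The comparison with 0.60 is only a yardstick. That value ("for the effect size of 0.60 and a significance level (alpha) of 0.050") comes from the paired t-test calculation, and the protocol does not power the week-30 comparison. With no affected participant the shift is zero.

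**The case against.** The strongest reply is that the criterion largely does the job it was given. Its stated reason is practical, not a promise that week-30 measurements will be free of post-operative effects. The window covers all of the treatment and the post-PBM assessment. The one remaining visit is protected by the attendance criterion, which already makes ineligible anyone whose booked operation would keep them away.

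The remaining case also needs several things together: an adult aged 18 to 35, major surgery booked more than six months ahead and falling within about four weeks, and recovery good enough to attend. No rate is available, and the size of the shift is assumed. Unbooked surgery could disturb week 30 in the same way.

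Most of this stands, and it limits the importance of the point. It does not remove it. Ability to attend is a different test from having undisturbed measurements, so the attendance criterion closes the gap only in part. The rarity of the case and the assumed shift bear on how large the problem is, not on whether the window is too short. That unbooked surgery remains possible is no reason to admit people whose surgery is already known.

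**Conclusion.** The point holds, as a minor one worth considering. Counted from baseline, the surgery exclusion ends about 3.9 weeks before the final assessment, and earlier still if the six months run from screening. Only the week-30 assessment and the last few pain-diary entries are exposed; the pre-to-post-PBM comparison, power and sample size are not.

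The gap itself follows from the document alone. The consequence does not: a movement of 0.04 to 0.08 SD in mean week-30 fatigue change, about 6% to 14% of the planning effect size, rests on exactly one affected participant and a surgical shift of 1 to 2 SD, neither of which the document supplies. Since few people would have surgery booked that far ahead, no effect at all is quite possible.

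**What to change.** In section 4.2, replace the six-month window with an exclusion of major surgery booked before the week-30 final assessment, about 7 months from baseline. Tying the window to the visit instead of a number of months also removes any doubt about whether it runs from screening or from baseline.

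The cost is one eligibility sentence and very few additional exclusions. Surgery not yet booked at screening would still not be prevented.
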